### Sample size

There is a limited amount of published data regarding the ideal size for pilot studies, and it has been commented that it seems that sample calculations may not be required for this type of study [58, 59]. An audit of registered studies found that the median sample size per arm for pilot studies was 30 (range from 8 to 114) [59]. Based on this evidence, we will recruit the median sample of 30 participants per arm.

### Recruitment and randomisation

#### Recruitment

All adult attendees who present to the participating ED and meet the inclusion criteria will be eligible to enter the study. Recruitment of study participants will occur in the ED by a research assistant (RA), which will ensure that the existing staffing levels at the ED research site are not affected. Recruitment will occur at the time of the patient’s presentation to ED, with due consideration given to their particular circumstances. Those who are indisposed, severely injured or severely distressed due to their injuries may not be approached; in such circumstances, guidance will be sought from attending ED staff on an individual basis.

Each potential participant will be provided with an information letter by a researcher, explaining the study. Those who agree to participate will be required to provide written consent.

#### Randomisation

Attendees who have moderate or high psychological distress will be randomised into intervention and control arms. Those with low psychological distress will be randomly selected (simple randomisation) to form a low distress comparison group for the purpose of measuring retention rates at follow-up and changes in K10 scores over time.

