#### Inclusion criteria

Inclusion criteria will include all alert and orientated English-speaking adults (over 18 years of age) who present to ED. Those attendees who have moderate or high levels of non-specific psychological distress, identified by the K10 (score 16–29) and do not require hospital admission will be eligible to enter the RCT study arm. They will be randomly allocated to either the intervention or control groups. Of the remaining participants, those with low psychological distress (score 10–15) will be enrolled in the “low-stress” control group.

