#### Exclusion criteria

Participants with very high K10 scores will be excluded from the study and will be given phone numbers of community mental health clinics. Other exclusions include ED attendees unable or unwilling to give consent or those unwilling to be contacted by telephone, people with a cognitive impairment or a learning disability, participants admitted to hospital as in-patients or already participating in mental health programmes. Participants will also be excluded if they are in police custody.

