### Follow-up

For all study participants, longitudinal follow-up will occur at 1, 3, 6 and 12 months by telephone interview. The purpose of a 12-month follow-up is to ensure the usefulness of longitudinal data by measuring the impact of the intervention over time [57]. We also want to track the natural course of mental health from all participants. The primary goal of using the K10 at each follow-up time-point is to measure changes in psychological distress over 12 months and to be able to compare data with other studies.

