#### Baseline

At recruitment, all consenting participants will be screened at time-point-a (T1a) and either included or excluded depending on K10 scores. Time-point-b (T1b) will commence post-screening, and data will then be collected from all eligible participants. Other data (such as primary ED diagnosis) will be collected from patient’s medical records.

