## Discussion

There is evidence regarding the effectiveness of screening and intervention in the ED for people with alcohol-use disorders [38–43]. However, screening and intervention in the ED for mental health problems has not been well investigated and has the potential to improve the quality of life of people who have moderate and high levels of psychological distress who might not otherwise seek mental health services. This project will provide evidence to inform the design of a larger study in the form of measurable outcomes regarding recruitment rates, retention rates at follow-up and satisfaction with the telephone intervention. The findings will enable practical questions to be answered about the most effective way to implement and recruit for a future study which will test the intervention on a larger scale. The findings will also provide a prospective longitudinal study of the natural history of at-risk and vulnerable population groups after their ED attendance and also information about the mental health of those who reported low levels of psychological distress at baseline.

Systematic screening of ED patients has the potential to bring about a major change in environment and culture. Currently, there is no routine follow-up of these attendees. Thus, it is possible that many of them—if they are not supported—will experience deterioration in their mental health, which will place an increased demand on future health services. Furthermore, for some patients, their mental health deterioration may lead to crisis situations such as extreme anxiety and depression and the possibility of other behaviours. Therefore, the longitudinal follow-up is essential to measure these possible changes.

Our project is unique in that it will pilot test an intervention that is not well tested in mental health contexts, and which is both practical and sustainable, and has the potential to integrate services from several healthcare disciplines. The project is targeted at the delivery level of healthcare services, focusing primarily on preventative health care and mental health promotion. Whereas previous research has focused on a single lifestyle problem group, e.g. alcohol users, or those with severe mental health problems, this study will focus on those with moderate and high psychological distress. In this context, we have found limited research to date that has investigated this population.

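### The screening K10 both forms the groups and serves as the only pre-treatment K10, so change from it in the low group, and the low versus moderate/high difference in change, partly reflects regression to the mean

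*Protocol article*

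**What the plan says.** **One K10 before treatment.** The Baseline section under Measures says that "all consenting participants will be screened at time-point-a (T1a) and either included or excluded depending on K10 scores". Attendees "identified by the K10 (score 16–29) and do not require hospital admission will be eligible to enter the RCT study arm", while "those with low psychological distress (score 10–15) will be enrolled in the “low-stress” control group". The Exclusion criteria add: "Participants with very high K10 scores will be excluded from the study". Table 2 schedules the K10 at screening (T1a) and at 1, 3, 6 and 12 months (T2 to T5), and marks it as not given at baseline (T1b).

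**What the later scores are for.** Under Randomisation, low scorers are randomly selected "to form a low distress comparison group for the purpose of measuring retention rates at follow-up and changes in K10 scores over time". The Follow-up section states: "The primary goal of using the K10 at each follow-up time-point is to measure changes in psychological distress over 12 months". It adds that the authors wish to follow the natural course of mental health in all participants. The Discussion expects a "prospective longitudinal study of the natural history of at-risk and vulnerable population groups", with information on the low group as well.

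**Mode.** Under Data collection, the ED assessments are on paper and the research assistant is absent while they are completed. Every follow-up is a telephone interview.

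**The concern.** The groups are non-overlapping bands of a score that carries measurement error and short-term fluctuation, and change is counted from that same score. People whose score was low by chance are over-represented in the low band. Because that band starts at the scale minimum of 10, its mean can be expected to rise on retest even if nobody's distress has changed. Randomly sampling within the band does not help, since the sample inherits the selection. A mode change over the same interval may shift each group further.

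At stake is a conclusion the article says it will draw. Upward drift in the low group could be reported as worsening after an ED visit, and a difference in change between the low and moderate/high groups as a difference in natural history. Pooling the MI arm into a natural-course description adds a separate problem, because that arm is treated.

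**Working it through.** The plan gives no figure for K10 change. Its only relevant number, 30 per arm, is the median of an audit of pilot studies and has no formula behind it, so there is nothing to reproduce. The size of the artefact can be bracketed.

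**Inputs from the protocol article**
- Bands: 10–15, 16–29, 30–50 (Screening).
- ED shares (Prevalence study): very high 10.1%, moderate/high almost 40%, so low = 100 − 40 − 10.1 = 49.9%.
- 30 per arm (Sample size).

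**Assumptions not in the article**
- Retest correlation r from 0.6 to 0.9 on the underlying normal (copula) scale, which is roughly 0.53 to 0.88 on the K10 scale.
- Shape of the K10 distribution: lognormal or gamma on K10 − 9.5, or flat within each band, each matched to the shares above and rounded to 10–50.
- No true change for anyone and no mode effect.

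**Method.** Draw X as standard normal and set Y = rX + √(1 − r²)·e. Convert both to K10 scores through the same distribution. Expected change in a band is the mean of (K10 from Y − K10 from X) among those whose first score falls in it. Gap = low change − moderate/high change. SE = √[(SD²low + SD²mod/high)/30]. Each row uses one million draws.

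| Shape | r | Low | Mod/high (16–29) | of which 22–29 | Gap | SE | Gap/SE |
|---|---|---|---|---|---|---|---|
| Lognormal | 0.6 | +2.10 | +0.10 | −2.00 | 2.00 | 1.77 | 1.13 |
| Lognormal | 0.8 | +0.99 | +0.27 | −0.68 | 0.72 | 1.31 | 0.55 |
| Lognormal | 0.9 | +0.48 | +0.20 | −0.21 | 0.28 | 0.94 | 0.29 |
| Gamma | 0.6 | +2.34 | −0.55 | −2.54 | 2.89 | 1.72 | 1.68 |
| Gamma | 0.9 | +0.57 | −0.06 | −0.59 | 0.63 | 0.92 | 0.68 |
| Flat in band | 0.6 | +2.73 | −0.89 | −2.34 | 3.62 | 1.89 | 1.91 |
| Flat in band | 0.9 | +0.73 | −0.18 | −0.59 | 0.91 | 1.05 | 0.87 |

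Worked line (flat, r = 0.6): the SDs of change are 5.51 and 8.78, so SE = √[(30.4 + 77.1)/30] = 1.89. The gap is 2.73 − (−0.89) = 3.62, and 3.62/1.89 = 1.91.

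The upper ends move by a tenth or two with how the flat bands are drawn. I therefore quote about 0.5–2.8 for the low group and 0.3–3.7 for the gap.

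**Category movement with no true change.** Between 14% (r = 0.9) and 30% (r = 0.6) of the low group reaches 16 or more. Of the moderate/high group, 18–34% falls to low and 8–13% rises to very high.

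**Why the whole moderate/high group moves little.** Its band is cut at both ends. Scores of 16–21 drift up and scores of 22–29 drift down, and the two largely cancel.

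**Sensitivity.** With the community shares in the Background (67/21/9/4%) and the lognormal and gamma shapes, the low group rises 0.3–1.5, the moderate/high group falls 0.2–1.8, and the gap is 0.5–3.3.

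**Timing of T2.** MI starts 48–96 hours after attendance and runs for up to two further weeks, so it ends by about day 4 + 14 = 18. T2, at one month, is therefore after treatment in the MI arm.

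**The case against.** The strongest reply is that this is a feasibility pilot. The main outcomes are recruitment, attrition and satisfaction, and none is touched. K10 effect is secondary. Data analysis calls the study underpowered, relies on description, urges caution over the regression/ANCOVA results, and sets no formal low versus moderate/high test of change. The Participants section justifies the low group by recruitment and retention alone. The size of the artefact rests on a correlation the article does not give, and may be under a third of a standard error. All of this stands and limits the weight of the point. It does not remove it, because Randomisation names K10 change as a purpose of the low group, and Follow-up and the Discussion state the natural-course reading.

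Two possible defences do not answer it. The Screening section's argument about the 30-day recall window addresses acute distress on the day, not selection on a fallible score. ANCOVA on the screening score cannot make the low and moderate/high groups comparable, because their bands share no scores.

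A reader might also infer more than the article supports:
- **That the distressed group will appear to improve.** Under the ED shares its mean moves −0.9 to +0.3, so even the sign depends on the assumed shape. Only the 22–29 band falls clearly, and no separate analysis of it is planned.
- **That the whole artefact falls before T2.** That requires a retest correlation that does not decline with time.
- **That the mode change affects the groups differently.** The article gives neither size nor direction, and a shift common to both groups cancels in the gap.
- **That K10 drift is to be used to justify the intervention.** The Discussion speaks of possible deterioration as a reason for follow-up.
- **That the MI comparison is biased.** Both randomised arms are selected alike and change mode together.

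**Conclusion.** The point holds for within-group change from screening and for the low versus moderate/high comparison of that change. It does not hold for the randomised contrast. With no true change, the low group would be expected to rise by about 0.5–2.8 points and 14–30% of it to leave the low band. The spurious gap in change is roughly 0.3–3.7 points, about 0.3–2 standard errors at 30 versus 30. These ranges rest on the assumed retest correlation of 0.6–0.9, the assumed distribution shapes, the ED shares from the earlier prevalence study, and a stable population mean. The mode effect on each group's own course comes on top and cannot be sized. The outcome is secondary and descriptive, so this is a matter of interpretation. It is worth correcting because the article commits to the interpretation and the correction needs no new data.

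**What to change.** Recruitment has closed and follow-up is underway (Trial status), so a second pre-treatment K10 is no longer possible. The analysis and reporting text should say:

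1. The effect of MI on K10 is judged only between the two randomised arms. T2 is not used as a baseline for that comparison, since it follows treatment.
2. Natural course is described only in the usual-care and low groups.
3. For those groups, K10 levels (mean, SD) and the percentage in each K10 band are reported at T2 to T5, all by telephone, with change measured from T2.
4. Change from T1a to T2 is not interpreted as deterioration or improvement, and is not compared between the low and moderate/high groups.
5. Starting at T2 removes the mode change and much of the regression, but some regression may continue if the retest correlation falls with time.

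The cost is analysis and wording only. The price is that the first month's change is no longer interpreted as natural course.

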#### Allocation concealment

Randomisation to groups will be done with computer-generated number tables. A stratified randomisation method will be used. Screened participants will be allocated to groups using a balanced block design to ensure that there are equal numbers of participants in the intervention and control group. A separate randomisation list will be drawn up for each of the health professionals (strata) that will be delivering the MI, to ensure that there are equal numbers of participants managed by each interviewer. This method will be used rather than a remote service to simplify procedures in the busy ED setting. The participant will not know at baseline whether they will have the MI intervention. Potential MI participants will be allocated by the health professional to treatment group or non-treatment group using an experiment to control a ratio of 1:1.

Follow-up at the designated time-points will be conducted by a RA who is not involved with data collection and will be blinded to the participant’s group allocation.

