### Intervention

The MI will be conducted by the telephone. The MI health professionals (one senior psychologist and three advanced-practice mental health nurses) will be provided with training sessions through an accredited training provider regarding the “spirit” of motivational interviewing. Clinical performance will be monitored by evaluating a random sample of interviews. MI will be assessed using the Motivational Interviewing Treatment Integrity 3.1.1 (MITI 3.1.1) [61]. Feedback of performance will be provided as necessary.

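### Allocation by the professionals who deliver MI, from per-professional blocked lists with no stated concealment device, leaves concealment unsecured for the only randomised comparison

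*Protocol article*

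**What the plan says.** All the relevant text is in the protocol article, mostly in the section Allocation concealment.

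- Sequence: "Randomisation to groups will be done with computer-generated number tables".
- Blocking: "Screened participants will be allocated to groups using a balanced block design". No block size is given.
- Lists: "A separate randomisation list will be drawn up for each of the health professionals (strata) that will be delivering the MI". The purpose given is an equal caseload for each interviewer.
- Remote allocation: "This method will be used rather than a remote service to simplify procedures in the busy ED setting".
- Allocator: "Potential MI participants will be allocated by the health professional to treatment group or non-treatment group", in a 1:1 ratio.
- Safeguards: "The participant will not know at baseline whether they will have the MI intervention", and follow-up is done by a research assistant blinded to group.

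The later section Intervention puts the number of MI deliverers at four: "one senior psychologist and three advanced-practice mental health nurses". The sections Recruitment and Data collection give recruitment, consent and baseline collection in the emergency department (ED) to a research assistant, a role described apart from the MI deliverers.

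**The concern.** Concealment means that whoever assigns a participant cannot know the next assignment until that participant is irrevocably in the trial. Here the assigning role is also the treating role, the lists are organised by treating professional, the blocks are balanced, and central allocation has been considered and declined. The two safeguards are blinding: one covers the participant at baseline, the other the outcome assessor. Neither acts on the allocator.

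MI against usual care in people with moderate or high distress is the only randomised comparison. The low-distress group is sampled from a different K10 range and is not assigned to a treatment. If people who seem receptive or easy to reach could be placed in the MI arm, MI satisfaction and MI-arm retention would look better than they are, and the K10 comparison would be confounded. The article says that the results will inform a larger trial, which might also inherit the procedure.

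**Working it through.** **No planned figure to reproduce.** The 30 per arm in the section Sample size is the median from an audit of pilot studies, not the result of a formula. The point is procedural. The arithmetic shows only how much an unconcealed blocked list could reveal.

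**Inputs**
- 30 per arm in two randomised arms: 2 × 30 = 60 randomised (Sample size; Table 1).
- Ratio 1:1 in balanced blocks (Allocation concealment).
- Block size: not stated. Sizes 2, 4 and 6 are assumed.
- Allocator's knowledge: not stated. Two cases are taken: (a) past assignments and block size are known; (b) the list can be read.

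**Share certain in advance, case (a).** Take a block of size 2m with m places per arm. An assignment is certain once the other arm's m places are used up. Each MI place comes after all m control places with probability 1/(m + 1), and the reverse holds for each control place. The expected number of certain places per block is 2 × m/(m + 1), so the share is 1/(m + 1).

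**Correct guesses, case (a).** The allocator always guesses the arm with more places left. For size 2: (0.5 + 1)/2 = 75.0%. For size 4 the four positions give 1/2, 2/3, 2/3 and 1, so 2.833/4 = 70.8%. Exact enumeration gives 68.3% for size 6.

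| Assumed block size | m | Certain in advance | Of 60, if all blocks are complete | Correct guesses |
|---|---|---|---|---|
| 2 | 1 | 50% | 30 | 75.0% |
| 4 | 2 | 33% | 20 | 70.8% |
| 6 | 3 | 25% | 15 | 68.3% |

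Under full concealment the share of correct guesses would be 50%. In case (b) every allocation is known, so the share certain is 100%.

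**What foreknowledge could affect.** Foreknowledge becomes bias only if someone can act on it.
- Enrolment: done by the research assistant. Selection at this step needs that person to know the lists, and the article does not say whether they can be seen.
- Assignment of people already enrolled: done by the treating professional. Which participant takes which place or list is not protected by anything stated.

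**Which outcomes are exposed.** The recruitment rate is a percentage of eligible people and does not depend on who enters which arm. Retention pooled over arms is largely insensitive. Retention by arm, MI satisfaction and the K10 comparison are exposed.

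**Whether the setting compels this method.** The first MI call comes 48–96 h after attendance, by telephone. Nothing in that schedule requires the assignment to be made on the ED floor, although the article does not say when it is made.

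**The case against.** The strongest reply is that the article does not show a failure of concealment. It does not say that each professional holds or reads a list, or chooses who fills a place. The sentence naming the allocator is garbled where it gives the ratio, and it may mean only that the professional carries out the next entry on a computer-generated list. Who keeps the list and how it is sealed are details that a condensed article often leaves to the full protocol. Consent and baseline belong to a separate research assistant, and no contact between professional and participant before allocation is described.

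Much of this stands. A reader might infer that allocation was in fact unconcealed, that all assignments were foreseeable, or that receptive people were steered to MI. The documents support none of these as fact. The percentages are conditional on an assumed block size and assumed knowledge.

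Two further inferences also fail. One is that 60 over four lists gives 15 each, an odd number that cannot split 1:1. Lists of 16, 16, 14 and 14 balance exactly, and 30 MI participants cannot be shared equally among four interviewers under any scheme. The other is that stratifying by interviewer is wrong because it balances no patient characteristic. Its stated purpose is caseload, and it can serve that.

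The reply does not remove the core. The section is not silent: it positively gives allocation to the treating role, declines a remote service, and offers only blinding as protection.

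**Conclusion.** The concern holds in a limited form: concealment is not secured by the procedure described, and the section's heading claims more than its text provides. The possible foreknowledge is 50%, 33% or 25% of allocations for blocks of 2, 4 or 6 if past assignments and block size are known, and 100% if the list is visible. How much bias, if any, resulted cannot be derived from the article.

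The exposure is to arm-specific retention, MI satisfaction and the secondary K10 comparison; the overall recruitment rate is not touched. The study is a pilot, and its Data analysis section already calls it underpowered for differences between groups and asks for caution with the regression results. Recruitment closed in May 2015, so only the reporting and the next trial can change. This should be fixed, but it does not invalidate the pilot's main feasibility results.

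**What to change.** **This trial, before outcomes are analysed**
- Compare each professional's actual allocations, with their order and dates, against the generated lists, and report every deviation.
- State that the treating professionals made the allocation and that concealment was not assured. If a safeguard existed, such as an independent list holder or sealed assignments, document it and say so instead.
- State the block size, and whether the recruiting research assistant could see the lists.

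The cost is one reconciliation of about 60 records and a less favourable description of the design.

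**The larger trial**
- A team member with no participant contact holds the list, with varied block sizes.
- Each assignment is released by telephone or email only after baseline (T1b) is complete and the participant is logged.
- The interviewer is assigned after allocation to MI. At this pilot's size a rota would give 8, 8, 7 and 7, which keeps caseloads near equal.
- Stratification by K10 band (16–21, 22–29) is optional.

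The cost is one call or message per participant (60 at the pilot's size), with no extra staff.

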### Participants

All adult patients presenting to the ED of a public hospital during the specified data collection period will be screened to participate in the study. Those who meet the screening criteria and consent to participate in the study will be able to enter the pilot RCT.

Based on psychological distress assessment, consenting ED patients will be categorised into three initial groups; those with:Moderate or high psychological distressLow psychological distressVery high psychological distress

Subsequently, group 1 will be randomly allocated to receive either the MI or usual care (usual care does not involve MI). A randomised sample of participants which report low psychological distress will form group 2 to represent a “low-stress” population control group. The inclusion of a “low-stress” control group will allow for further assessment of recruitment strategies and retention of participants. Group 3 will be excluded from the study (but will be provided with advice to contact a health professional). Thus, there will be three arms to the study (see Table 1).

**Table 1 Tab1:** Randomisation of groups

Condition 1		Intervention
Group 1	Moderate/high psychological distress	MI plus usual care
	Moderate/high psychological distress	Usual care
Group 2	Low psychological distress	Usual care

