### Intervention

In this study, the MI will be used to encourage and motivate study participants to seek and obtain further assistance for their psychological needs. The overall spirit of MI is described as collaborative and evocative, and honours patient autonomy. A MI follows four guiding principles: resisting the fighting reflex, understanding and exploring the patient's own motivations, listening with empathy and empowering the patient, and encouraging hope and optimism [56]. The MI intervention has been designed to be pragmatic in that it will be tailored to each participant’s individual circumstances and needs.

Following recruitment, all participants will be provided with standard care, i.e. usual care from their ED attendance. Participants who are randomised into the intervention arm will receive an initial MI, delivered by telephone interview 48–96 h after their ED attendance, with up to three additional MIs by telephone during the following 2 weeks. Each MI is expected to last up to 60 min (a total of not more than 4 h for each study participant).

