### Measures

The main outcome of this pilot trial is the identification of recruitment and retention rates from baseline to all follow-up time-points. Table 2 summarises the measures, instruments and their administration timetable. Instruments have been carefully selected due to their specific relevance to the population of interest. General measures have been selected due to their widespread use, robust reliability and validity testing and availability of norm values [54, 62–67].

**Table 2 Tab2:** Measures

Measure	Instruments	T1a	T1b	T2	T3	T4	T5
		Screening	Baseline				
Demographics	Demographics	X	✓	X	X	X	X
Mental health and well-being	K10 [54]	✓	X	✓	✓	✓	✓
	DASS 21 [62].	X	✓	X	X	✓	✓
	Satisfaction with Life Scale [63].	X	✓	✓	X	X	✓
	WHO-BREF [64].	X	✓	X	✓	X	✓
Moderators	Readiness to change stage [65].	X	✓	X	X	X	X
	General self-efficacy scale [66]	X	✓	✓	X	X	✓
Outcomes	Health service usage and health-related actions survey [67].	X	✓	✓	✓	✓	✓
	MI satisfaction questionnaire	X	X	✓	X	X	X

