#### Follow-up

Satisfaction of MI will be assessed with a specifically designed tool 5-item Likert scale questionnaire.

Pre- and post-intervention measures will be used to assess outcomes including motivation, confidence and health-seeking behaviour and utilisation, mental health and well-being and subjective quality of life.

All participants will be followed-up at four time-points: 1 month (T2), 3 months (T3), 6 months (T4) and 12 months (T5). Data will be collected by a registered nurse RA via telephone. Data will be input initially via onscreen software, into an Excel database, where they will be checked and verified for transcript errors before importing into an SPSS (version 21) database for analysis.

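### The follow-up assistant is said to be blinded, yet the 1-month telephone follow-up includes a satisfaction questionnaire that only motivational-interviewing participants can answer

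*Protocol article*

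**What the plan says.** The blinding claim stands under Allocation concealment: "Follow-up at the designated time-points will be conducted by a RA who is not involved with data collection and will be blinded" to group allocation.

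The mode of follow-up is given twice. The first Follow-up section says that "longitudinal follow-up will occur at 1, 3, 6 and 12 months by telephone interview". The later one, under Measures, adds "Data will be collected by a registered nurse RA via telephone".

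That later section also introduces the satisfaction instrument: "Satisfaction of MI will be assessed with a specifically designed tool 5-item Likert scale questionnaire". Table 2 lists the "MI satisfaction questionnaire" and ticks it at T2 (1 month) only. At T2 the table also ticks K10, the life satisfaction scale, the self-efficacy scale and the health service usage survey. K10 is ticked at all four follow-ups.

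Only one arm has anything to rate. The first Intervention section says "Participants who are randomised into the intervention arm will receive an initial MI, delivered by telephone interview 48–96 h after their ED attendance", and the Participants section notes that "usual care does not involve MI".

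**The concern.** Someone who asks a participant how satisfied they were with their MI calls either knows already that the participant had them or finds out from the reply. A blinded assessor cannot do this and stay blinded. Because the questionnaire falls at the first of four follow-ups, whatever is learned there can carry into the later ones.

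Two outcomes are exposed. The effect on K10 is a named secondary outcome. K10 is a self-report scale, but at follow-up it is obtained in a live call, where delivery and probing can vary. Attrition is a main outcome, and the Data analysis section measures it by whether the telephone survey was completed at each time-point. Completion depends partly on how hard the caller tries, and that effort can differ between people known to have had MI and the rest.

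The pilot exists to plan a larger trial. A procedure described as blinded that unblinds at the first contact could be carried forward under the wrong label.

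**Working it through.** No figure in the plan needs to be reproduced. The check sets the sections side by side and follows the consequences.

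**Step 1: do the statements meet at T2?**
- Allocation concealment: an assistant blinded to allocation conducts follow-up at the designated time-points.
- Both Follow-up sections: the time-points are 1, 3, 6 and 12 months, and collection is by a research assistant by telephone.
- Table 2: the MI satisfaction questionnaire belongs to the 1-month time-point.
- Nowhere in the article is there a second collector, a self-completed form or an order of questions.

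They meet by inference. No sentence says outright that the blinded assistant administers this form, but it is the only reading for which the article names a person and a mode. The remark that this assistant takes no part in data collection probably refers to baseline collection in the ED; otherwise it would conflict with the sentence that has an assistant collecting the follow-up data.

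**Step 2: can the form be given without breaking the blind?**
- If only MI participants are asked, the assistant must know the arm before or during the call.
- If everyone is asked, the answers show who had MI.

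Either way, the assistant ends the T2 call knowing.

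**Step 3: which assessments are exposed?** K10 is collected at 4 follow-ups; the satisfaction form is at 1 of them, the first.

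| Circumstance | K10 assessments exposed |
|---|---|
| Same assistant calls later, satisfaction asked after K10 at T2 | T3, T4, T5: 4 − 1 = 3 of 4 |
| Same assistant calls later, satisfaction asked before K10 at T2 | T2 to T5: 4 of 4 |
| Different assistant from T3, with no access to T2 answers, satisfaction asked after K10 | 0 of 4 |
| Different assistant from T3, with no access to T2 answers, satisfaction asked before K10 | T2 only: 1 of 4 |

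The article fixes neither the order nor whether one individual makes every call. These counts assume that the assistant learns the arm during the call. An assistant told the arm beforehand is unblinded for the whole T2 call, whatever the order.

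**Step 4: how many people?** The planned size is 30 per arm. If a proportion r of the MI arm completes T2, 30 × r people are identified directly, so at most 30. The other T2 completers are known only not to have had MI. At planned sizes these come from 30 randomised controls plus 30 low-distress participants, so the assistant cannot tell from this which of the two groups a person belongs to.

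**Step 5: what about retention?** If the arm is learned from the answers, it is learned only after the participant has been reached. Call effort at T2 is then untouched, and T2 non-responders are not revealed. Call effort at T3 to T5 is exposed for those who completed T2. T2 retention is affected only if the assistant is told the arm beforehand, which the article does not say.

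**The case against.** The strongest reply is that a condensed article need not say who hands out one short form or in what order. Table 2 gives timing only. The sentence introducing the satisfaction tool names no collector, and the sentence about telephone collection comes two paragraphs later. The full protocol may route the form elsewhere. This stands as a limit on certainty. It does not remove the conflict, because the article makes a specific blinding claim and publishes a schedule which, read together with its own account of follow-up, defeats it.

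The reply can add that little depends on the blind. K10 is a fixed-item self-report scale and a secondary outcome. The Data analysis section describes the study as underpowered, plans mainly descriptive analysis and urges caution about its regression results. Recruitment rate, the first main outcome, is settled before any follow-up call. All of this is fair and keeps the point moderate. No size of bias can be derived from the document.

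A reader might infer more: that blinding is wholly absent for K10 and retention from T2 onward, that one assistant certainly makes every call, or that the randomised controls are unmasked by elimination. The article supports none of these. The order of questions and the continuity of the caller are not stated. T2 call effort is affected only by prior knowledge of the arm. Knowing that someone had no MI does not separate a control from a low-distress participant.

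**Conclusion.** On its plain reading the plan contradicts itself: a blinded assistant conducts a T2 follow-up that contains questions only the MI arm can answer. The conclusion rests on one inference, that the form is part of the telephone follow-up, because no other collector or mode is named.

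If the same assistant makes the later calls, K10 and call effort at T3, T4 and T5 are not blinded for those who completed T2. K10 at T2 is also affected if satisfaction is asked first. Direct identification reaches at most 30 people. The point should be put right, but it does not threaten the recruitment outcome, and no confirmatory conclusion depends on it in a pilot of this size.

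**What to change.** **For T2 contacts still to come, and for the larger trial:**
- Collect the satisfaction questionnaire outside the outcome call, either self-completed by post or link, or by someone who makes no outcome calls.
- Ask K10 first in every call.
- Use the same call-attempt rule in both randomised arms.

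The cost is about 30 separate forms and a script change. The downside is a possibly lower response rate for satisfaction, itself a main outcome. If a second person collects the form, that person's time must be found in an unfunded study.

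**For T2 calls already made:** Trial status says that recruitment closed in May 2015 and follow-up was under way. The last 1-month calls would fall in about June 2015, so for most participants only this part is likely to be usable.
- State that assessor blinding cannot be claimed after the T2 satisfaction questionnaire, unless the full protocol shows that the form took another route.
- Record the assistant's guess of allocation at the remaining calls.
- Keep the K10-first order and the common call-attempt rule for those calls.
- Interpret differences in K10 and retention between the randomised arms with this in mind.

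These steps need a few sentences in the report and one extra item per call.
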